**Methods:**

We report the protocol of an open‐label, randomized, pilot study that will be conducted at a single Canadian center. Our primary objective is to evaluate the safety and efficacy of microwave treatment (Swift^®^ System, Emblation Ltd, Scotland, U.K.), administered at three different dosing regimens, in 45 patients with mild‐to‐moderate distal subungual onychomycosis. Our secondary objective is to identify an optimal dosing regimen, if any, to better inform the conduct of a future pivotal trial. Patients will be randomized (1:1:1) to undergo either 9 treatment sessions (5 weekly sessions plus 4 monthly sessions), 7 treatment sessions (3 sessions every 2 weeks plus 4 monthly sessions), or 12 treatment sessions every 2 weeks. At each session microwave energy will be applied in 3‐s intervals at 7–9 Watts, repeated up to 5 times at each treatment position on the nail. Overlapping treatment positions are used to ensure sufficient coverage of the infected area. Patients will be enrolled in the trial over a 12‐month period. Efficacy will be evaluated based on visual improvement and mycology testing results. Adverse events will be recorded throughout the entire study period.

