Patients will be evaluated at enrolment, which includes medical history, concomitant medications (prescriptions, over‐the‐counter medications, supplements), onychomycosis disease duration and treatment history, and toenail measurements (i.e. nail thickness, total affected nail surface area and lowest distance between the affected nail area to the proximal nail fold) (Figure 1); Flyers/posters, online and radio advertisements will be used to increase enrolment. Once a patient provides written informed consent and meets the eligibility criteria, one affected hallux will be sampled for mycology testing (i.e., fungal culture, polymerase chain reaction [PCR] and direct potassium hydroxide [KOH] microscopy). Patients testing PCR and/or fungal culture positive for dermatophytes will be eligible to join the study.

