### Treatment procedures

2.3

At enrolment, one affected hallux will be designated as the treatment target; up to 3 additional ‘non‐target’ toenails may also receive treatment. Prior to treatment, all visual and photographic assessments will be performed, in addition to sampling for mycology testing, as per the study schedule (Figure 1).

During each treatment session, toenails will be prepared by the clinician. Nails will be soaked in warm water for a minimum of 5 min to aid hydration and microwave energy absorption thereby generating heat in the nail plate and nail bed; then they will be cleaned with an antiseptic solution and allowed to dry. Microwave energy will be applied locally at a pre‐specified dose of 7–9 W for up to 3 s (i.e., one “burst”); treatment may be initiated at 9 W for up to 3 s with further adjustments of power and time settings depending on patient tolerability. Up to 5 additional bursts, spaced approximately 5‐s apart and subject to patient tolerability, may be administered in the same location and then repeated at a new location to ensure complete coverage of the nail surface. The affected nail area for treatment is chosen by the clinician administering the microwave energy and is concentrated on the proximal margin of discolouration and then distally as needed. The dose, duration and number of repetitions from each session will be recorded.

Investigators will follow the operation manual of the microwave device (Swift^®^ System, Emblation Ltd.). A new disposable tip will be fitted to the applicator probe used during each treatment session of up to 15 min from the first delivery of microwave energy. Ambient operating temperature should be between 10 and 30°C.

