### Data analysis

2.8

As a pilot study, sample size calculations were not performed; a sample size of 15 patients per treatment group was selected to provide sufficient preliminary data on treatment safety, tolerability and efficacy in onychomycosis patients.

The per‐protocol and intention‐to‐treat populations will be included for safety and efficacy analyses. Descriptive statistics will be conducted for subject demographic and baseline parameters including sex, Fitzpatrick skin type (I‐VI) and fungal species. All AEs will be presented by description, category, frequency, severity and causality; differences in incidence between Groups A and C will be tabulated. Statistical analyses will be performed if there are sufficient data points available.

Statistical analyses for the difference in proportion of subjects achieving a pre‐specified efficacy endpoint between treatment groups will be conducted using the Chi‐square test; *p* < 0.05 will be considered statistically significant. Nail measurements will be converted to the mean increase in clear nail, both in terms of clear nail length from the proximal nail fold and clear nail surface area. The mean increase in clear nail, mean increase in clear nail as a function of the number of treatments and energy dose administered, mean increase in clear nail as a function of the number of visits attended and mean pain scores at treatment visits will be analysed using ANOVA or the Kruskal–Wallis test depending on data distribution; *p* < 0.05 will be considered statistically significant. Additional correction measures will be performed at the statistician's discretion.

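### The unadjusted energy-response analysis in section 2.8 can show a false dose-response, because baseline affected area may drive both energy received and nail gained

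*Protocol article*

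**What the plan says.** Section 2.8 (Data analysis) lists, among its analyses, "mean increase in clear nail as a function of the number of treatments and energy dose administered". Nail measurements become a mean increase in clear nail, "both in terms of clear nail length from the proximal nail fold and clear nail surface area", so the outcome is an absolute gain and not a share of the diseased area. These analyses "will be analysed using ANOVA or the Kruskal–Wallis test depending on data distribution", and p below "0.05 will be considered statistically significant". No covariate is named. The only further provision is that "Additional correction measures will be performed" at the statistician's discretion.

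The documents describe coverage in two ways. Abstract, Methods: "Overlapping treatment positions are used to ensure sufficient coverage of the infected area". Section 2.3 (Treatment procedures): bursts "may be administered in the same location and then repeated at a new location to ensure complete coverage of the nail surface". Section 2.3 also lets the clinician choose the affected area to treat, starting at the proximal edge of the discolouration and moving distally where needed. Power and time are adjusted to tolerability.

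Section 2.1 has these measured at enrolment: "nail thickness, total affected nail surface area and lowest distance between the affected nail area to the proximal nail fold". Section 2.2 offers non-responders at month 6 or month 9 three further monthly sessions.

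**The concern.** The randomised factor is the treatment schedule. The energy a patient actually receives also depends on power, burst time, repetitions and possibly the number of positions treated, and these may reflect baseline severity. If more positions are treated on a more diseased nail, and a more diseased nail has more area to regain, then lesion size is a common cause of exposure and outcome. An unadjusted comparison of energy levels would then credit energy with a difference that belongs to lesion size. Replacing the ANOVA with a regression on total energy alone would leave the same bias.

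The trial's secondary objective is to find the best dosing regimen, if there is one, for a pivotal trial. A false energy-response signal reported beside the randomised comparison could colour that choice.

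**Working it through.** The plan gives no energy total, effect size or power figure, so there is none to reproduce. The check has three parts.

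**1. How far each driver of energy can vary (from the documents).**
- Affected share of the nail (Table 1): 75/20 = 3.75-fold.
- Sessions by group (section 2.2): 12/7 = 1.71-fold.
- Power (section 2.3): 9/7 = 1.29-fold.

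If positions follow the infected area, lesion size can outweigh the randomised schedule in total energy.

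**2. False-positive rate when energy has no effect.** From the documents: 39 enrolled (45 planned), sessions 9/7/12, affected share 20% to 75%. Assumptions:
- Affected share is uniform over that range; nail size has mean 100 units and SD 15.
- Energy = sessions × positions × tolerability factor. The factor is uniform 7/9 to 1 (power) times uniform 0.6 to 1 (bursts and time).
- Area is measured with error SD 5 units at each time.
- Where gain scales with area, gain = affected area × a share with SD 0.25 and the mean shown. Where it does not, gain averages 18 units (SD 10), capped by the affected area.
- Patients are split into thirds of energy, since section 2.8 does not say how energy is grouped.

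There were 2,000 runs per scenario. The Monte Carlo standard error is √(0.05×0.95/2000) = 0.005 at the nominal rate and √(0.42×0.58/2000) = 0.011 at a rate of 0.42.

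| Positions follow | Gain | ANOVA, N=39 | Kruskal–Wallis, N=39 | ANOVA, N=45 |
|---|---|---|---|---|
| Affected area | mean 60% of area | 0.75 | 0.73 | not run |
| Affected area | mean 40% | 0.42 | 0.40 | 0.49 |
| Affected area | mean 20% | 0.14 | 0.12 | not run |
| Affected area | mean 10% | 0.09 | 0.07 | not run |
| Half tied to area | mean 40% | 0.17 | 0.16 | 0.21 |
| Whole nail | mean 40% | 0.06 | 0.05 | 0.07 |
| Positions not counted | mean 40% | 0.04 | 0.04 | 0.05 |
| Affected area | unrelated to area | 0.05 | 0.04 | 0.05 |
| Affected area | none in anyone | 0.05 | 0.05 | 0.05 |

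A second simulation used a 250 mm² nail (CV 15%), energy per position with CV 25%, and a cleared share of mean 30%, SD 15 points. At N=39, Kruskal–Wallis rejected in 59% when energy was proportional to affected area and in 22% when half tied to it.

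With three retreatment sessions added for the poorer half of responders (an assumption), N=39, mean gain 40%:
- Energy tracking area: the mean correlation of energy with gain falls from +0.34 to +0.10, and ANOVA rejects in 0.09.
- Energy not counting positions: the correlation falls from 0 to −0.37, and ANOVA rejects in 0.49, a false inverse dose-response.

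**3. Candidate remedies.**
- *Baseline affected area as covariate* (first simulation). Where energy and gain (mean 40%) both track area, rejection falls from 0.42 to 0.06 (N=39) and from 0.49 to 0.07 (N=45). The cure is incomplete when area is measured with error: 0.09 to 0.10 if gain is unrelated to area, and 0.18 to 0.20 if nobody gains. It does not rescue an analysis that includes retreatment energy (0.35 to 0.36).
- *Dividing both energy and gain by baseline affected area.* Here absolute gain averages 30 mm² (SD 15, capped by area), with the 250 mm² nail and energy CV 25%. Under whole-nail coverage the planned Kruskal–Wallis test rejects in 4.5% and the ratio version in 49%. With energy unrelated to lesion area the figures are 5.1% and 55%. The shared denominator creates the association.
- *Comparing the randomised groups.* Rejection stays at 0.04 to 0.06 throughout.

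The length outcome was not simulated; its link to affected area is less direct.

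**The case against.** A reader might infer that energy rises with lesion size by design, that a 75% nail receives 3.75 times the energy of a 20% nail, and that the analysis therefore will show a dose-response. The documents do not support that reading, for four reasons.

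- **Coverage.** Only the abstract ties positions to covering the infected area. Section 2.3 speaks of covering the nail surface and leaves the treated area to the clinician. Under whole-nail coverage the error is 0.06 to 0.07.
- **Definition of energy.** Section 2.3 uses the word dose for a power setting. It says that dose, duration and repetitions are recorded, without naming positions. If positions are not counted, the error is nominal.
- **Outcome.** A larger lesion raises the ceiling on gain but does not make actual gain proportional to lesion size. If nobody improves, the error stays at 0.05.
- **Direction.** Retreatment pulls the other way, so the sign of the net bias is not fixed.

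It can also be said that covariates are often left to an analysis plan, which is not shown here, that section 2.8 allows further corrections, and that dosing frequency is answered by the randomised groups. No passage says the energy analysis will itself choose the pivotal regimen.

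These points stand against the strong reading. They do not remove the concern: section 2.8 names the exposure, the absolute outcome, the tests and the threshold. A discretionary correction does not fix an adjustment in advance. Full proportionality is not needed either, since half-tied energy already gives 0.17 to 0.21 at 40% mean gain.

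**Conclusion.** The concern holds in conditional form. The planned test of absolute gain against non-randomised energy is open to confounding by baseline affected area. When energy has no effect, its false-positive rate runs from about 5% to over 60% (75% in the most extreme scenario). The high end needs three things together: energy dose counts positions, positions follow the infected area, and gain scales with that area. If any one fails, the error is near nominal. Energy counted after month 6 adds confounding in the opposite direction through retreatment of non-responders. The rates depend on the listed assumptions and show a range, not a forecast. The matter is worth correcting because the change is small and baseline affected area is already measured, but it concerns an ancillary analysis and does not touch the randomised comparison.

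**What to change.** In section 2.8:
- Analyse gain at day 168 on energy delivered to the target nail up to day 168, in a regression with baseline affected area, randomised arm and baseline nail thickness as covariates. Stopping at day 168 keeps retreatment energy out.
- Do not divide exposure and outcome by the same baseline area.
- State whether energy dose counts treatment positions, and confirm that the session records allow a total for the target nail separately from non-target nails.
- Reconcile the abstract and section 2.3 on what the positions are meant to cover.
- Label the analysis exploratory, and base the regimen comparison on the randomised groups.

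The cost is slightly more analysis work, one derived variable and a few degrees of freedom from 39 patients. Some bias remains if area is measured with error. The spread of gain is likely to widen with lesion area, so ordinary standard errors may be somewhat optimistic. The dose-response may also look weaker than in the unadjusted analysis. If positions were not recorded, a total that counts them cannot be rebuilt and the report should say so.

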### Study intervention

2.2

On day 0, patients will be randomized (1:1:1) to one of three treatment groups (Groups A–C) based on a computer‐generated randomisation schedule generated prior to the start of the study (Figure 1). Group A will undergo nine treatment sessions, which includes the first session at day zero followed by four weekly sessions then four monthly sessions. Group B will undergo 7 treatment sessions, which includes the first session at day 0 followed by sessions every 2 weeks for 2 sessions then 4 monthly sessions. Group C will undergo 12 treatment sessions, which includes the first session at day 0 followed by sessions every 2 weeks.

Non‐responders at the end of the month 6 visit (day 168) or month 9 visit (day 252) as judged by the US FDA recommended endpoint (i.e., “temporary increase of clear nail”) will be given the option to undergo retreatment once per month for 3 months up to month 9 or month 12, respectively (Figure 1).^13^ Subjects who do not wish to undergo retreatment will be asked to return for month 9 and month 12 visits.

Tinea pedis is a common co‐infection seen in onychomycosis patients^17^; in this study, patients presenting with concomitant tinea pedis, at the investigator's discretion, may be provided with topical antifungal agents for treating affected skin areas. Toenails will be strictly avoided. No local anaesthetic, petroleum jelly nor metallic‐based topical treatments (e.g., aluminium chloride, silver nitrate) are to be used in the toenail areas during this study. Concomitant use of oral antifungal agents is not permitted.

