### Study assessments

2.4

All enroled subjects will be assessed until month 12 for the evaluation of efficacy and safety endpoints, including interim treatment visits (Figure 1). Clinical response will be evaluated based on in‐person assessments and photographic images of the treated hallux, both in terms of the affected nail area and nail length. Mycology testing will be performed at baseline, day 84 (month 3), day 168 (month 6), day 252 (month 9) and day 336 (month 12).

Incidence of adverse events (AEs) will be recorded throughout the entire study period; each AE will be graded based on severity (mild, moderate, severe) and relatedness to the study intervention. The investigator will deem an AE as ‘expected’ if it's consistent with previous reports in the literature,^10^, ^11^, ^18^ which includes local application site reactions such as pain, bruising, heat sensitivity and tingling. Burns, blisters, or nail disfigurement will be considered as ‘unexpected’ AEs. Any new clinically relevant findings deemed by the investigator will be reported as an AE. Patients will be asked to report their pain level—categorised as none, mild, moderate or severe—before treatment, during treatment, and 10‐min post‐treatment. Additionally, patient‐reported outcomes (PROs) will be recorded at pre‐specified timepoints of which patients will be asked to rate (a) how their daily activities are affected, (b) how their lifestyle activities (e.g. sports, hobbies) are affected and (c) how their mood is affected.

Subjects who wish to discontinue from treatment will be asked to complete all remaining study assessments as planned. The principal investigator may withdraw a subject from the study if there is significant protocol non‐compliance, AEs or other medical conditions such that the continued study participation would not be in the interest of the subject, or subject meeting the exclusion criteria during the study period. If a subject fails to return for 2 scheduled visits, and is unable to be contacted (through multiple telephone calls and letters), the site staff will make a reasonable effort to ascertain reason(s).

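### The analysis of clear-nail gain by number of treatments has no cut-off at month 6; if retreatment sessions, offered only to non-responders, are counted, it is biased towards less clear nail with more treatment

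*Protocol article*

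**What the plan says.** Section 2.8 (Data analysis) lists several analyses of nail measurements. One is "mean increase in clear nail as a function of the number of treatments and energy dose administered"; another relates the same outcome to visits attended. Both, with the plain mean increase, "will be analysed using ANOVA or the Kruskal–Wallis test depending on data distribution", and p < "0.05 will be considered statistically significant". The section does not say at which visit the gain is read, which sessions count, or whether the exposure is the schedule assigned or the sessions received.

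Section 2.2 (Study intervention) assigns 9, 7 or 12 sessions by randomisation to Groups A, B and C. It then provides that patients judged non-responders on the clear-nail endpoint at month 6 or month 9 "will be given the option to undergo retreatment once per month for 3 months up to month 9 or month 12, respectively". Those who decline stay in follow-up: "Subjects who do not wish to undergo retreatment will be asked to return for month 9 and month 12 visits".

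Section 2.4 (Study assessments) says "All enroled subjects will be assessed until month 12 for the evaluation of efficacy and safety endpoints", so clear-nail measurements after retreatment will exist.

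**The concern.** Up to month 6 the number of sessions is set by randomisation, apart from missed visits. After month 6 a patient can gain sessions only by having too little clear nail. Clear nail is also the outcome of the analysis, so over that part of follow-up the exposure is a consequence of the outcome. Neither ANOVA nor Kruskal–Wallis on session counts can separate this selection from an effect of treatment.

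The trial's secondary objective is to identify an optimal dosing frequency for a pivotal trial. An analysis of response against amount of treatment will be read in that light. If retreatment sessions are counted, it could understate or reverse a real benefit of more sessions.

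**Working it through.** **1. When the assigned sessions end.** From section 2.2, taking a month as 28 days (day 168 is month 6):
- Group A: days 0, 7, 14, 21, 28, then 56, 84, 112, 140 (9 sessions).
- Group B: days 0, 14, 28, then 56, 84, 112, 140 (7 sessions).
- Group C: every 14 days from day 0 to 11 × 14 = 154 (12 sessions).

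The month 6 window opens on day 168 − 7 = 161. All assigned sessions therefore precede it, and every later session is a retreatment.

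**2. What the counts then mean.** With 0, 3 or 6 extra sessions the totals are:
- Group B: 7, 10, 13
- Group A: 9, 12, 15
- Group C: 12, 15, 18

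If no session is missed, totals of 10, 13, 15 and 18 contain only patients who were non-responders. A total of 12 mixes Group C patients without retreatment and Group A non-responders retreated once. With at most one round, totals of 10 and 15 are still made up only of non-responders.

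**3. Size without a ceiling on gain.** The article gives no effect size, SD or retreatment uptake, so these are assumptions. There were 15 patients per arm and 1,000 trials per scenario. With b the assigned sessions (mean 9.33) and β the true effect in mm per session:
- gain at month 6 = μ + β(b − 9.33) + N(0, SD 3 mm)
- retreatment if gain < 6 mm (the length criterion in section 2.5) and the patient accepts; tested again at month 9
- each later 3-month step adds 1 mm + 3β if retreated + N(0, SD 1 mm)
- month 12 gain is regressed on b + 3 × (rounds received)

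Results with β = 0, as mean slope in mm per session and share of trials negative and significant:

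| Mean month 6 gain μ | Uptake 30% | Uptake 60% | Uptake 100% |
|---|---|---|---|
| 3 mm | −0.21; 20% | −0.33; 56% | −0.57; 96% |
| 5 mm | −0.30; 38% | −0.45; 85% | −0.61; 100% |
| 6 mm | −0.32; 37% | −0.48; 89% | −0.60; 100% |

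The nominal figure in the negative direction is 2.5%. With 13 per arm (39 enrolled ÷ 3), μ = 5 mm and 60% uptake, it is 80%.

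With β = 0.2 the fitted slope is −0.02 to −0.50. With β = 0.5 it is −0.36 to +0.27. It lies below the truth in all 27 scenarios and is negative in 23. The four positive ones all have β = 0.5 and uptake of 30% or 60%.

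**4. Size with a ceiling.** Gain cannot exceed the nail length involved at baseline, and section 2.5 counts complete clearance as response when less than 6 mm was involved. A second model has 13 per arm, gain at month m = m·r + N(0, SD 0.5 mm), r ~ N(0.9, SD 0.45) mm per 28 days truncated at 0, 70% acceptance and no true effect. The cap is uniform on 4–10 mm or 3–12 mm:

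| Setting | Slope | Negative and significant | Kruskal–Wallis rejects |
|---|---|---|---|
| No cap, two rounds | −0.90 | 95% | 94% |
| Capped, two rounds | −0.17 to −0.19 | 23–30% | 9–12% |
| Capped at 4–10 mm, one round | −0.13 | 14% | 9% |

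Over a wider set of capped assumptions the trend was negative and significant in about 12–69% of trials. With a true benefit of 0.23 mm per session, the capped slope is negative in 71–81% of trials but significantly so in only 7–13%.

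**5. After the correction.** In the step 3 model, month 6 gain against assigned sessions has a mean slope of −0.011 to +0.002 when β = 0, about 0.19 to 0.21 when β = 0.2 and 0.49 to 0.51 when β = 0.5. In the uncapped step 4 model, two-sided rejection with no true effect is 4–6%.

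**The case against.** The best defence is that section 2.8 is silent rather than wrong. Every endpoint defined as an increase in clear nail is read at month 3 or month 6 (section 2.5; section 2.6, first efficacy endpoint). Months 9 and 12 carry mycological and effective cure. A month 6 reading is natural, would be unbiased, and may be what an analysis plan not shown here specifies. This stands as a limit on the claim. It does not remove it: the article fixes outcome, exposure and tests, follows everyone to month 12, and nowhere excludes retreatment sessions.

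A reader might infer that the trial will show more treatment giving less clear nail, almost with certainty. The documents do not support that, for four reasons:
- No visit is named.
- Section 2.2 does not say that one patient may have both retreatment rounds.
- Rates near 95% come from a linear trend, not the planned non-directional tests, and from gains averaging 12 × 0.9 = 10.8 mm at month 12 with no ceiling.
- With a strong true effect and partial uptake the slope can stay positive, though too small.

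It is also fair that the analysis supports no primary or listed secondary endpoint, and that the randomised-group comparisons already address dosing frequency. That lowers the severity.

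**Conclusion.** The concern holds conditionally. If sessions after month 6 are counted against a later clear-nail measurement, the relation is biased towards less clear nail with more treatment and may reverse. The direction follows from the design and appeared in every setting examined.

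The size does not follow from the article. With no true effect, the trend stand-in is negative and significant in roughly 12–100% of simulated trials, depending on uptake, growth rate, ceiling on gain and one or two retreatment rounds. The lower end, with gain capped at baseline involvement, is the more cautious guide; there Kruskal–Wallis rejects in about 9–12%.

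A day-168 analysis and the comparisons of randomised groups are not affected. Severity is moderate: the analysis is supportive in a pilot, but it bears on the choice of regimen.

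**What to change.** In section 2.8, for the analysis by number of treatments and energy:
- Set day 168 as the outcome visit, and count only treatments and energy delivered before that assessment.
- Use the randomised schedule (7, 9 or 12 sessions) as the main exposure, with received sessions and energy as supportive.
- Report clear-nail change after retreatment separately, measured from the start of retreatment.
- Apply the same cut-off to the analysis by visits attended, because retreatment visits would raise that count in the same way.
- State that power and time settings are adjusted for tolerability (section 2.3), so the relation of received energy to outcome is exploratory even before day 168. The cut-off does not cure this.

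The cost is a few sentences of analysis wording. Data after month 6 are left out of this one analysis and reported separately. The randomised-schedule part largely repeats the group comparison already planned, which is the price of an unconfounded exposure.
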